### SGJP decoction

The formula comprises 11 herbs, including Radix Bupleuri (Chai Hu) 5 g, radices paeoniae alba (Bai Shao) 10 g, Tuckahoe (Fu Ling) 15 g, Turmeric Root Tuber (Yu Jin) 10 g, etc. The indication of the formula is liver stagnation and spleen deficiency pattern, including symptoms of fatigue, chest tightness, poor appetite, and abdominal distension, depressed, irritable and wiry and slippery pulse.

The procedure of preparing the SGJP decoction is as follows: firstly, all herbs are tipped into an earthenware pot with 1000 mL cold water and soaked for about half an hour. Secondly, give a boil with strong fire and then turn soft fire to simmer about 30 min until decoction reduces to 200 mL. Thirdly, the decoction is poured out and the same herbs with same water are boiled again for another 200 mL decoction over heat. Finally, these two times of decoction is mixed well together. Patients in the case group should take 200 mL of the decoction two times a day.

### Outcome measurements

#### Primary outcome

The primary outcome was complete response to therapy, defined as complete biochemical remission at the patient’s last visit of observation period and the absence of predefined steroid-specific side effects throughout observation period (moon face, central obesity, buffalo hump, diabetes and increased intraocular pressure, etc.). Biochemical remission was defined as complete normalization of aminotransferase levels including IgG.

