**Methods:**

A prospective non-randomized study on AIH will be conducted between October 2015 and June 2017 in Guangdong Provincial hospital of Chinese medicine. Eligible AIH patients will be classified as the case group (*n* = 66) and the control group (*n* = 66) based on the interventions. Patients taking Shu-Gan-Jian-Pi Decoction combined with prednisone and azathioprine will be in the case group and those taking prednisone and azathioprine will be in the control group. The whole study will last 48 weeks, including a 24-week observation period and a 24-week follow-up period. The primary outcome was complete response to therapy, defined as complete biochemical remission at the patient’s last visit of observation period and the absence of predefined steroid-specific side effects throughout treatment.

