## Methods/design

### Study design

This is a prospective, non-randomized, controlled study. One-hundred and thirty two AIH patients visited in Guangdong provincial hospital of Chinese medicine at the first time will be enrolled and divided into two groups with a case: control ratio of approximately 1:1. While patients in the control group received the steroid standard therapy, patients in the case group are treated with combination treatment of SGJP decoction and the steroid therapy. Both of the treatment and follow-up period will be for 24 weeks. The details of the flow chart of this trial are shown in Fig. 1.

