### Patient population

A total of 132 AIH patients, who fulfill the screening criteria, is being enrolled and followed up between October 2015 and June 2017. According to the patients’ preference, the eligible AIH patients will be divided into two groups: the case group (to receive SGJP Decoction combined with low dose prednisone and azathioprine, *n* = 66) or a control group (to receive low dose prednisone and azathioprine, *n* = 66).

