### Inclusion criteria

(1) All the patients had either a first diagnosis of AIH or were experiencing relapse after a previous diagnosis of AIH based on histology findings within 12 months before screening. (2) TCM syndrome type: liver stagnation and spleen deficiency. (3) Patients fulfill indications for treatment: serum aspartate aminotransferase (AST) ≥ 10-fold upper limit of normal (ULN) levels; or Serum AST ≥ 5-fold ULN and gammaglobulins ≥ twice ULN; or Bridging necrosis or multiacinar necrosis on histopathological examination (4) aged from 18 to 65 years.

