### Exclusion criteria

(1) co-infection with hepatitis virus or human immunodeficiency virus; (2) evidence of advanced liver diseases, such as decompensated cirrhosis, severe hepatitis, or hepatic carcinoma; (3) evidence of serious uncontrollable diseases, such as heart, brain, kidney or gastrointestinal primary disease, etc.; (4) recent treatment with drugs with known liver toxicity; (5) pregnancy or lactation; (6) parenteral administration of blood or blood products within 6 months before screening.

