#### Data monitoring board

Two supervisors who are not members of the end-point committee should be assigned to contact and visit the researchers regularly to supervise the trial progress. Through this monitoring process, it can be ensured that it is conducted, recorded and reported in accordance with the protocol and standard operating procedures. In addition, the researchers should agree to cooperate with the supervisors to ensure that any problems found and resolved.

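### The side-effect half of the primary outcome is scored as absence, with no reference to baseline, although relapsed patients may enter with steroid features already present and patients choose their group

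*Protocol article*

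**What the plan says.** Complete response has two halves (protocol article, Primary outcome). One is biochemical remission at the last visit of the observation period. The other is "absence of predefined steroid-specific side effects throughout observation period (moon face, central obesity, buffalo hump, diabetes and increased intraocular pressure, etc". The abstract gives the second half as "the absence of predefined steroid-specific side effects throughout treatment". Neither version mentions onset, worsening or baseline, and no item carries a criterion.

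The other sections that bear on this are:

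- **Inclusion criteria.** Newly diagnosed patients are eligible, and so are those who "were experiencing relapse after a previous diagnosis of AIH based on histology findings within 12 months before screening".
- **Exclusion criteria.** The general medical exclusion is "evidence of serious uncontrollable diseases, such as heart, brain, kidney or gastrointestinal primary disease, etc". Diabetes, cushingoid features and raised intraocular pressure are not named.
- **Patient population.** Allocation follows the patients' "preference, the eligible AIH patients will be divided into two groups".
- **Background.** Relapse is described as frequent once medication is stopped. Relapse and corticosteroid side effects are given as reasons why patients turn to traditional Chinese medicine.
- **Study design and Interventions.** "This is a prospective, non-randomized, controlled study". Only the case group takes the decoction, and no dummy is described.
- **Data monitoring board.** The only mention of independent outcome review is "Two supervisors who are not members of the end-point committee". The committee's task and blinding are not described.
- **Discussion.** Propensity scores are planned to balance the groups. No covariates are named.

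**The concern.** An endpoint that counts treatment harm should count what happens after treatment starts. A rule of plain absence also counts what the patient brought along. That matters little if nobody can enter with a listed feature, but here the eligibility criteria let such patients in. The Background's own account of relapse after stopping medication makes earlier steroid treatment likely in the relapsed patients.

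If affected patients were equally common in both groups, the rule would only add fixed failures and cost power. Allocation by preference removes that reassurance. If patients who have had trouble with steroids tend to choose the decoction, the case group starts with more patients who cannot succeed. The opposite imbalance would flatter the decoction.

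A second, weaker issue sits on top. Moon face, buffalo hump and central obesity, as written, are judged by looking. Patients and treating doctors know who takes the decoction, so scoring could differ between groups unless someone without that knowledge classifies the events.

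**Working it through.** **1. What the article gives.** It has no response rate, no side-effect rate, and no count of relapsed or diabetic patients, so it has no figure on this point to reproduce. The only usable number is the evaluable sample of 110, set by expert agreement. With 15% dropout, 110 / 0.85 = 129.4, rounded up to 130, against the stated 132, which is close enough. For illustration, 110 / 2 = 55 per group.

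**2. The rule applied to eligible patients.**

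| Patient at entry | Result under the text |
|---|---|
| Relapsed, earlier steroids, no listed feature now | Not affected; can respond |
| Relapsed, moon face or buffalo hump persisting from earlier steroids | A steroid side effect is present during observation: fails as written, whatever the study treatment does |
| Controlled diabetes or raised intraocular pressure that began on earlier steroids | As above |
| Controlled diabetes that predates any steroid | On the list, but arguably not a steroid side effect: depends on the assessor |

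The second and third rows follow from the wording. The fourth is a real ambiguity: two assessors could score the same patient in opposite ways.

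**3. Effect of pre-existing features (all rates assumed).** Let *p* be the response rate among patients without a feature at entry and *f* the fraction who have one and therefore fail. Observed response is *p*(1 − *f*).

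- Uneven, no true effect, *p* = 0.50, *f* = 0.20 in the case group and 0.05 in the control group: 0.50 × 0.80 = 40.0% against 0.50 × 0.95 = 47.5%, a false difference of 7.5 points against the decoction. Swapping the fractions reverses the sign.
- Present in one group only, *p* = 0.50, 55 per group, two-sided 0.05, normal approximation with pooled null variance: an excess of 10, 20 or 30 points gives a rejection rate of 8%, 18% or 36% instead of 5%.
- Equal in both groups: no false difference. A true 40% against 60% has 56% power with *f* = 0. With *f* = 0.20 it becomes 32% against 48%, with 40% power.

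**4. Effect of scoring that differs by group (all rates assumed).** Let remission be *R*, the true side-effect rate *s* in both groups, and let side effects be under-scored by *d* in the case group. With the two halves independent, response is *R*(1 − *s*) in the control group and *R*(1 − *s* + *d*) in the case group. For *R* = 0.80, *s* = 0.30, *d* = 0.10 this is 56% against 64%, with a rejection rate of 14%. Over *R* = 60–80% and *s* = 30–50%, *d* of 10 points gives 10–14%, and *d* of 20 points gives 24–42%. In patient numbers, five mis-scored patients of 55, all otherwise in remission, move the case-group result by 5 / 55 = 9.1 points.

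Steps 3 and 4 can push in opposite directions, and nothing makes them cancel.

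**The case against.** The strongest reply is that this is a condensed article and that the words carry more than a hostile reading allows. Much of that stands.

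- **A reader might infer that anyone with earlier steroid exposure or diabetes fails from the first day.** The text does not say so. Exposure alone causes no failure; only a persisting feature does. The items are called steroid-specific side effects, so diabetes that predates steroids can reasonably be left out.
- **A reader might infer from the trailing abbreviation in the list that items can be added once the group is known.** The list is called predefined. The article also shortens fixed lists in this way elsewhere: the SGJP decoction section announces 11 herbs and names four. A closed list with criteria may well exist in the full protocol. What remains is that the printed definition should show it.
- **A reader might infer that unblinded staff score the items.** No section says who scores them, and the end-point committee leaves room for independent assessment. Diabetes and intraocular pressure are also measurable. The text supports a risk of biased scoring and does not show that it occurs.
- **Propensity scores are planned.** They could balance baseline features if these are included, and the choice of covariates belongs in the analysis plan. But balance does not repair the definition: a patient with a persisting feature would still be unable to respond.

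The reply does not reach the central point. The article fixes the rule as absence and admits patients in whom absence may be impossible from the start.

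**Conclusion.** The concern holds in this limited form. As written, a steroid feature that persists from earlier treatment makes complete response impossible, and the text leaves open whether other pre-existing conditions count. With allocation by preference, and steroid side effects a stated motive for seeking herbal treatment, an uneven spread of such patients is plausible and would bias the primary comparison. Undescribed assessment of appearance-based items adds a separate risk.

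Neither the size nor the net direction can be derived from the document. The 7.5 and 9.1 points and the rejection rates above rest on assumed rates and show only what moderate imbalances could do with about 55 patients per group. They should not be quoted as the bias of this trial.

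**What to change.** - Record every listed item at baseline, and count only new onset or worsening after baseline.
- In the endpoint text, replace the trailing abbreviation with the full predefined list.
- Have the end-point committee mentioned under Data monitoring board classify events from records with the treatment group removed.
- Include baseline presence of listed features and earlier steroid exposure in the propensity score announced in the Discussion.

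The cost is a change of endpoint wording, one baseline checklist and some extra record preparation for the committee. Patients with a pre-existing feature will contribute less information on that item. Because the Trial status section says recruitment is under way, baseline status for patients already enrolled would have to come from existing records, and the change should be documented before any comparison by group.

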#### Secondary outcomes

Secondary outcomes include the proportion of patients whose g-glutamyl transpeptidase (GGT) and total bilirubin (TBIL) levels decrease more than 50% after 4-week treatment as well as the GGT and TBIL normalization rate, the remission rate of patients’ clinical symptoms and the occurrence rate of the immunosuppressive agents’ side effects after 24-week treatment.

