#### Sample size and statistical methods

This prospective study is intended to evaluate the efficacy and safety of the combination treatment of SGJP Decoction and steroid standard therapy on AIH. Since there is still no enough reliable data to accurately calculate the sample size for our study, 20 hepatology experts in Chinese medicine or integrative medicine with more than 20 years clinical experience were asked for advice. After two rounds of meetings with these experts, we agreed that 110 patients should be sufficient to gather enough information in order to plan such a clinical trial. And 132 cases are needed if there is a dropout rate of 15%.

The statistical analysis for this study will be performed using SPSS software version 19.0 (SPSS Inc., Chicago, IL, USA). Data will be presented as mean and standard deviation, or frequency and percentages. Comparisons will be conducted between the case group and the control group, also between pre-treatment and post-treatment in each group. For normally distributed variables, means will be compared by using t-tests (two-tailed), and nonparametric variables will be analyzed using Pearson chi-squared tests or Fisher exact tests. All *P*-values will be two-tailed. A P-value of less than 0.05 will be considered statistically significant.

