## Discussion

AIH is known as a harmful disease with a high mortality which can easily progress to cirrhosis or liver failure. Prednisone plus azathioprine is considered the mainstay of therapy in the current recommendations for AIH therapy originate from this era. However, it does not provide good benefits for AIH patients because of its serious side effects. In this case, TCM has been popular used to treat AIH in China with good efficacy, low costs and small side effects. However, there is no rigorous and objective testing. What is more, Western medicine and TCM approaches have been used together to reach great effect worldwide [15]. Therefore, we conduct this study to explore whether the combination treatment of an empirical Chinese Herbal formula (SGJP Decoction) and steroids standard therapy could improve the clinical management of AIH.

This prospective study aims to explore the efficacy and safety of SGJP Decoction combined with steroid standard therapy on AIH. The achievement of this trial will provide evidence-based data for SGJP Decoction, which could provide good benefits for AIH patients. More over, the success of this study would represent justification and impetus for a large scale clinical study to further consolidate the evidence for the use of SGJP Decoction in AIH patients.

Our study also has several limitations that require consideration. Firstly, the case and control groups are not randomly assigned. However, we will use a new method of statistical analysis to make up for this shortage, the causal inference method, which has been used in previous randomized controlled trials [16]. In this method, propensity scores can balance the case and control group by limiting the confounding factors so that can help researchers to evaluate the interventions more accurately. Secondly, the sample size is still too small. However, the study produced critical data for sample size calculation of future study. And control of confounding variables, appropriate randomization, sufficient sample size and longer treatment period should be included in future study.

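### The week-4 GGT and TBIL outcomes are listed only as the proportion falling by more than 50%; a baseline-adjusted log-scale comparison would be more precise at little cost (minor, secondary outcomes)

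*Protocol article*

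**What the plan says.** Under Outcome measurements, Secondary outcomes, the protocol article lists "the proportion of patients whose g-glutamyl transpeptidase (GGT) and total bilirubin (TBIL) levels decrease more than 50% after 4-week treatment". The same sentence continues "as well as the GGT and TBIL normalization rate", so the other GGT and TBIL outcome is also a rate. The remaining listed efficacy outcomes (complete response as primary outcome, remission of clinical symptoms) are likewise yes/no per patient.

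Sample size and statistical methods states that "nonparametric variables will be analyzed using Pearson chi-squared tests or Fisher exact tests", which in practice covers the proportions. It also provides for means with SDs, t-tests on normally distributed variables and pre/post comparisons within each group, but names neither GGT nor TBIL there. The significance rule is "A P-value of less than 0.05 will be considered statistically significant", two-sided.

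On size, the same section reports an expert consensus: "we agreed that 110 patients should be sufficient to gather enough information in order to plan such a clinical trial". The Discussion adds: "Secondly, the sample size is still too small. However, the study produced critical data for sample size calculation of future study". It also says that propensity scores will be used to balance the two groups, which are formed by patient preference.

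**The concern.** Both markers have a numerical baseline and week-4 value. Once cut at 50%, a 49% fall counts the same as a rise, and a 51% fall the same as a 95% fall. The article gives no reason for this cut. The guideline it cites is used for diagnosis and steroid therapy, and normalization is a separate outcome.

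Two things are at stake. The first is precision, in a study that calls its own sample too small. The second is the usefulness of the results for planning a later trial, which the article names as a purpose. A between-group ratio with its residual SD serves that purpose better than a proportion passing an unexplained threshold.

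**Working it through.** **The plan's own figure.** The only sample-size figure that can be recomputed is the dropout inflation: 110 / (1 − 0.15) = 129.4, so 130. The stated 132 is within 2 patients of this. The base of 110 is a consensus and cannot be derived. The article states no power for any outcome.

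**Inputs from the article.** 110 evaluable patients at about 1:1, so n = 55 per group (66 if all enrolled patients are analysed); two-sided alpha 0.05; chi-squared or Fisher for proportions.

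**Inputs assumed, because the article gives none.** The log of week-4 over baseline is normal with equal SD in both groups. The standardised difference between groups is d. A share p0 of controls meets the 50% cut.

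**Formulas.**
- Full scale: two-sample t-test, noncentrality d·√(n/2).
- After the cut: case-group responder rate p1 = Φ(Φ⁻¹(p0) + d). Power = Φ{[(p1 − p0) − 1.96·se0] / se1}, with pooled mean p̄ = (p0 + p1)/2, se0 = √[2p̄(1 − p̄)/n] and se1 = √[p0(1 − p0)/n + p1(1 − p1)/n].

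**Worked case, n = 55.** The t-test has 80% power at d = 0.539.
- p0 = 0.40: p1 = Φ(−0.253 + 0.539) = 0.612; se0 = 0.0953; se1 = 0.0932. Power = Φ[(0.2124 − 0.1869)/0.0932] = Φ(0.274) = 0.608.
- p0 = 0.20: p1 = Φ(−0.842 + 0.539) = 0.381; se0 = 0.0866; se1 = 0.0848. Power = Φ[(0.1811 − 0.1697)/0.0848] = Φ(0.134) = 0.554 (from unrounded values).

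| Control responders | Case responders | Power after cut | Loss from 80% (points) |
|---|---|---|---|
| 20% | 38.1% | 55.4% | 24.6 |
| 30% | 50.6% | 59.7% | 20.3 |
| 40% | 61.2% | 60.8% | 19.2 |
| 50% | 70.5% | 59.6% | 20.4 |
| 60% | 78.6% | 56.2% | 23.8 |

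For effects with 50%, 70% and 90% full-scale power (d = 0.377, 0.478, 0.624), the losses over the same control rates are 15 to 20, 19 to 25 and 17 to 22 points. With 66 per group, re-solving d for the same full-scale power, the losses are nearly identical.

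**Simulation.** With 4,000 runs per setting at n = 55 and d = 0.534 (the 80% point by the normal approximation), the losses were 24.6, 20.3, 19.9 and 28.7 points at control rates of 20%, 30%, 50% and 70%.

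**Wider range, n = 55, control rates 10% to 80%, normal approximation.**

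| d | Loss (points) |
|---|---|
| 0.2 | 5 to 9 |
| 0.3 | 11 to 19 |
| 0.4 | 17 to 29 |
| 0.5 | 20 to 37 |
| 0.6 | 18 to 40 |
| 0.7 | 13 to 38 |
| 0.8 | 8 to 32 |
| 1.0 | 1 to 21 |

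The loss is small where power is already very low (d = 0.2) or near its ceiling (d = 1.0 with control rates of about 20% to 50%). It is largest for moderate effects when the cut lies far from the middle of the distribution.

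**Information retained for small effects.** The ratio φ(z)²/[p0(1 − p0)], with z = Φ⁻¹(p0), is 0.49 at p0 = 0.20 and 0.64 at p0 = 0.50. The cut therefore discards roughly a third to a half of the information.

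**The case against.** A responder rate is a legitimate clinical outcome and matches the other listed efficacy outcomes. The condensed article may omit both the rationale for the cut and any supplementary continuous summaries. That stands, and it is why the missing rationale is not itself a fault here. The point concerns the outcome definition that the article does fix.

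The power model is also a simplification. The inclusion criteria rest on AST, gammaglobulins and histology and do not require raised GGT or TBIL, so a uniform normal shift in the log ratio is unsupported, and the true loss could be larger or smaller. The comparison of a t-test with chi-squared also ignores the propensity-score adjustment that the Discussion intends. Finally, the wording could mean that both markers must fall by more than 50%, a joint outcome that the calculation does not cover. These limits stand.

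Three stronger readings are tempting, and the documents do not support them:
- **A fixed loss at the planned size.** A reader might take 15 to 25 points as a property of the design. It depends on an effect, an SD and a responder rate that the article does not give.
- **No mean or SD will be available.** The statistical methods section provides for means and SDs and does not exclude GGT or TBIL. It simply does not assign them.
- **A real week-4 effect will probably be missed.** In the 80% scenario the chance of a miss rises from 20% to about 39% to 45%, so detection remains more likely than not.

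**Conclusion.** The point holds as a minor improvement to secondary outcomes. The article defines the week-4 GGT and TBIL outcomes only as proportions and assigns no full-scale comparison to either. Under the stated model with 55 per group, an effect detectable with 80% power on the full scale keeps about 55% to 61% after the cut at control rates of 20% to 60%, a loss of about 19 to 25 points. Over d = 0.2 to 1.0 and control rates of 10% to 80%, the loss is about 1 to 40 points. All of these figures rest on assumed inputs.

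No power is claimed for these outcomes, and the primary outcome and its analysis are unaffected. What would be gained is a more precise week-4 comparison, and a geometric-mean ratio and SD for the future sample-size calculation that the Discussion names.

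**What to change.** In Secondary outcomes, define the week-4 comparison on log week-4 GGT and log week-4 TBIL, each analysed separately. In Sample size and statistical methods, specify a linear model for each marker with group, the log baseline value and the propensity score intended in the Discussion. Report the ratio of geometric means with its 95% CI and the residual SD. Keep the rate of falls above 50% as a descriptive supplement, and state whether that rate is per marker or requires both.

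The cost is one extra model per marker on values already collected, with no new visits, tests or patients. The downside is that a ratio of geometric means is slightly less intuitive to clinicians than a responder rate, which is why the rate stays in the report.

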**Discussion:**

This trial will evaluate the efficacy and safety of Shu-Gan-Jian-Pi Decoction combined with prednisone and azathioprine on AIH patients. The achievement of this trial will provide evidence-based data for Shu-Gan-Jian-Pi Decoction, which could provide good benefits for AIH patients.

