In recent years, more and more researchers try to explore the efficacy and safety of combination treatment of steroids and Chinese herbal medicine in AIH patients. Fortunately, a number of clinical studies have proved the positive efficacy of TCM in Chinese AIH patients [7–9], such as alleviating liver inflammation; reducing side effects of corticosteroids and improving TCM signs and symptoms. But most of these studies were case reports or expert experience, or did not report strict inclusion and exclusion criteria, or had small sample size. Moreover, even the formulation of TCM was in the form of capsule or injection in some of these trials. Thus, current studies do not provide sufficient evidence to support the effectiveness of TCM in the treatment of AIH. So we have made a further research on the issue to explore whether the combination treatment of TCM and steroid standard therapy could improve the clinical management of AIH. Shu-Gan-Jian-Pi (SGJP) Decoction, made by famous traditional Chinese medicine doctor [name], is a popular used Chinese herbal formula in Guangdong province of China, which has demonstrated the effect of improving efficacy and reducing side effects of corticosteroids in AIH patients. This recipe, coming from the Golden mirror of medicine (a famous textbook of TCM), is widely used in treating chronic liver disease patients with pattern of live stagnation and spleen deficiency for more than 30 years. The results of previous clinical studies and animal experiments [10, 11] of SGJP Decoction provide the evidence that it has the effects of immunomodulatory and anti-liver-inflammation. However, previous clinical studies were retrospective study or focus on the patients with autoimmune diseases combined with hepatitis B, not on the AIH itself. Therefore, we conduct a prospective study to evaluate the efficacy and safety of SGJP Decoction combined with steroid standard therapy in AIH patients.

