#### Safety outcomes

The results of a routine blood test, routine urine test, routine stool test, renal function test and electrocardiogram are assessed before and after the treatment to ensure the safety of this study. Further more, a urine pregnancy test or serum human chorionic gonadotropin test must be done before enrolling a women patient of childbearing age.

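### Safety of the added decoction is an aim, but clinical adverse events are compared only as steroid or immunosuppressant side effects, and liver tests are not a safety measure

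*Protocol article*

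**What the plan says.** Safety of the combination is stated as an aim three times: in the Background ("to evaluate the efficacy and safety of SGJP Decoction combined with steroid standard therapy in AIH patients"), in Sample size and statistical methods ("intended to evaluate the efficacy and safety of the combination treatment of SGJP Decoction and steroid standard therapy on AIH") and in the Discussion paragraph of the Abstract ("This trial will evaluate the efficacy and safety of Shu-Gan-Jian-Pi Decoction combined with prednisone and azathioprine on AIH patients").

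Three parts of Outcome measurements bear on harm:

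- **Primary outcome.** Complete response needs biochemical remission at the last observation visit and "the absence of predefined steroid-specific side effects throughout observation period". Moon face, central obesity and diabetes are among the examples. Remission means normal aminotransferases and IgG.
- **Secondary outcomes.** The one side-effect rate listed is "the occurrence rate of the immunosuppressive agents" side effects, after 24 weeks. GGT and total bilirubin appear as efficacy measures: a fall of more than 50% after 4 weeks, and normalisation.
- **Safety outcomes.** This section reads: "The results of a routine blood test, routine urine test, routine stool test, renal function test and electrocardiogram are assessed before and after the treatment", with the purpose "to ensure the safety of this study".

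The statistics section says that comparisons are made between the groups, and before against after treatment within each group.

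**The concern.** Both groups take prednisone and azathioprine; the planned difference is the decoction. The safety question is therefore what the decoction adds to, or takes away from, the harm seen on background therapy. An outcome defined by the side effects of the background drugs answers the second half of that question. It answers the first half only where harm from the herbs happens to look like, or is recorded as, a background-drug effect.

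The imbalance runs in the direction the authors expect, since the Conclusions say that the study will verify a reduction in steroid dose and steroid side effects. A table built on these outcomes could show fewer side effects in the case group while clinical events newly caused by the decoction stayed outside it.

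Liver safety matters most. Patients enter with active liver inflammation, the formula has 11 herbs, and the exclusion criteria already bar recent use of drugs known to be toxic to the liver.

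**Working it through.** No arithmetic applies: the only derived figure in the article is the sample size, and the point does not depend on it. The check is to set the outcomes side by side and ask which events each one admits.

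| Outcome (section) | What it counts | Tied to a drug? | When |
|---|---|---|---|
| Side-effect part of complete response (Primary outcome) | Predefined steroid effects | Yes, steroid | Throughout the observation period |
| Side-effect rate (Secondary outcomes) | Effects of the immunosuppressive agents | Yes, immunosuppressants | After 24 weeks |
| Tests and ECG (Safety outcomes) | Blood, urine, stool, renal function, ECG | No | Before and after treatment |
| Aminotransferases, IgG (Primary outcome) | Normal or not | No, but an efficacy measure | Last observation visit |
| GGT, bilirubin (Secondary outcomes) | Fall of more than 50%; normalisation | No, but an efficacy measure | After 4 weeks; after 24-week treatment |

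**Clinical events.** The secondary side-effect rate can be read in two ways.

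1. *By attribution:* an event counts if it is judged to be caused by an immunosuppressant. An event put down to the herbs, or to no drug, is then left out.
2. *By event type:* known side-effect types are counted in both groups whatever the cause. A herb-related event of a listed type then counts; one of an unlisted type does not.

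On either reading some clinical events attributable to the decoction fall outside both side-effect outcomes. Serious events and withdrawals because of an event are not named as outcomes on either reading.

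**Laboratory and ECG findings.** These apply to both groups without regard to drug. With the general statement on group comparisons, they could reveal haematological, renal or cardiac harm from any cause. They do not register a symptom or a clinical event as such, nor an abnormality that comes and goes between the two assessments.

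**Liver findings.** Liver tests are absent from the safety list. There are two cases to follow:

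- *Aminotransferases raised at the last observation visit.* The patient is a non-responder. The result is the same whether the disease failed to respond or the liver was injured by treatment, and whether the value is just above normal or above baseline.
- *A rise during treatment that resolves before that visit.* The patient can still be a complete responder, and the rise enters no outcome.

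GGT and bilirubin behave in a similar way. Persistent injury would lower the normalisation rates, but it would appear as missing benefit and not as harm.

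**The case against.** The strongest reply is that harm from the decoction is not invisible. The Safety outcomes section follows directly and is not restricted to any drug. Persistent liver injury would lower the primary response rate and the GGT and bilirubin normalisation rates in the case group. This stands, and it rules out any claim that such harm is counted nowhere. It does not reach clinical events, and it does not separate liver injury from non-response.

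The second reply is that a journal article condenses a fuller protocol, where adverse-event recording, serious-event reporting and the handling of early leavers may well be set out. This stands too: the absence of those procedures here is no finding. But recording events elsewhere does not change how the published outcomes are defined, and it is those definitions that decide what is compared between groups.

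The third reply is that the phrase on immunosuppressive agents may mean event types and not case-by-case attribution. That is possible, and the point holds under both readings.

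The last reply is that recruitment has begun, so a change now comes late. That is a limit on the remedy, and it should be reported with the results.

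**Conclusion.** The point holds as one about outcome definition. Safety of the added decoction is an aim, yet clinical adverse events enter the outcomes only as effects of the background drugs. Beyond before-and-after tests and an ECG, no stated outcome compares clinical events of any cause between the groups. Liver tests serve efficacy only, so injury cannot be told from treatment failure and a transient rise is lost. Its size cannot be put as a number from the article. It should be corrected, because the safety half of the objective is otherwise answered only in part.

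The conclusion assumes that the article states the outcomes in full and that the general sentence on group comparisons covers the safety tests.

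A reader might infer three stronger things, and the article supports none of them:

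- *That staff who know the group decide attribution.* The article does not say who judges causes, and the masking of the end-point committee it mentions is not described.
- *That the 15% who may drop out have no test after treatment.* The 15% is a planning assumption, and nothing is said about the samples of early leavers.
- *That an upper limit for zero events in 66 exposed patients measures the defect.* Such a limit depends on the number of patients and would be the same under a perfect adverse-event definition.

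**What to change.** In Secondary outcomes and Safety outcomes:

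1. Define the clinical safety outcome as all adverse events through week 24 in both groups, including serious events and withdrawals because of an event, regardless of the agent to which they are attributed. Give the proportion of patients by group and the difference with a 95% confidence interval.
2. Keep the immunosuppressant side-effect rate as a subset of that outcome.
3. Add aminotransferase worsening from baseline as a safety outcome, using values already measured. The article gives no schedule of aminotransferase tests between baseline and the last observation visit. Where interim values exist they should be used, since only they can show a transient rise; where they do not, the outcome is limited to worsening at the last visit and should say so.

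The cost is slightly more recording and one more table, with no new procedure. Because the trial is already recruiting, capture may be incomplete in patients treated before the change. The report should state from which date all events were recorded and, if capture differed, show the results for patients enrolled before and after that date.
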